## Patients and methods

### Patients

We will conduct a retrospective study based on the analysis of files of patients followed in the Reference Center for Rare Diseases in Ophthalmology since 2018. We will only retain files in which the presence or absence of sphincter disorders is clearly mentioned. Although this symptom is systematically sought during consultations and day hospitalization by the referring physician of the Centre, there is a risk that some patients may not have declared it.

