## Introduction

Wolfram syndrome (WS) is a rare, autosomal recessive neurodegenerative pathology, the prevalence of which is estimated at 1/830,000 people (1/55,000–1/700,000 according to Barrett) (Barrett and Bundey, 1997). WFS1 is the main gene involved, responsible for type 1 WS (WS1) (MIM #222300), while the CISD2 gene is responsible for type 2 WS (MIM #604928) (Amr et al., 2007, Inoue et al., 1998). WS1 is characterized by the association of insulin-dependent diabetes and optic atrophy, both occurring before the age of 16 according to EuroWABB guidelines (EuroWAAB, 2014). Other symptoms may occur, such as diabetes insipidus, sensorineural hearing loss, neurological damage, and urinary tract abnormalities (Karzon et al., 2018, Washington University Wolfram Study Group, 2013, Urano, 2016). These vesico-sphincter disorders during WS1 are linked to multiple factors: neurological disorders responsible for a neurological bladder, diabetes insipidus, insulin-dependent diabetes (Ribière et al., 2013, Rove et al., 2018). These well-known disorders are subjects of numerous studies that describe them or discuss their management.

Surprisingly, the French patient association reported to our rare disease center dedicated to Wolfram syndrome that some patients presented with ano-sphincteric dysfunction, which they had never dared to discuss. These symptoms were never mentioned because the patients and their family were not specifically sought during consultations and were very embarrassed. This condition must be considered as debilitating for the patients, who are deeply ashamed of it. Furthermore, these patients believed that these symptoms should not be linked to their condition since they are not part of the "classic list" of symptoms and were never brought up at family meetings. A preliminary study was conducted based on a questionnaire sent to patients with Wolfram syndrome followed in our rare disease center or to patients, who attended to therapeutic education sessions. In this study, 45.95%. of the WS1 patients complained with such severe and disabling problem ([name], 2025). The importance of this frequency allowed us to conclude that these ano-sphincteric disorders are a real and new symptom of WS. It must be taken into account by physicians and treated as such.

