## Method

The method we intend to implement will be based on data from literature concerning the possible neurological origin of fecal incontinence. A neurological mechanism will be considered given the pathophysiology of WS, which is a neurodegenerative condition (Barrett et al., 1993, Barrett and Bundey, 1997, Urano, 2016). It is well known that neurological or ENT symptoms, such as swallowing disorders, will appear during the course of WS (Marshall et al., 2013). However, in order not to overlook variations related to patient mutations, we will add to this study a genetic component. Marshal and other authors demonstrated that the severity of the symptoms during WS is related to the type of mutations harbored by the patients (Marshall et al., 2013)^.^.

In order to determine the mechanism of ano-sphincteric disorders, we will divide the patients into two subgroups according to the presence or absence of ano-sphincteric disorders.

According to this generic mechanism, we will collect different parameters that will be used in the analyses: the duration of the WS, the duration of insulin type I diabetes, the values of glycosylated hemoglobins over this period, the age of patients as well as their visual acuity at first occurrence of ano-sphincteric disorders and the presence of vesico-sphincter disorders, swallowing disorders or sleep apnea (Hoekel et al., 2014).

Firstly, we intend to characterize the severity of the WS in each patient as the occurrence of ano-sphincteric disorders. To that end, we have planned to consider more specifically three parameters from patient’s files for a multi-factorial analysis. We will consider the age of our patients when ano-sphincteric disorders were mentioned for the first time as well as the duration of WS and the duration of insulin type I diabetes at the time of the first mention of this symptom. This duration will be calculated from the age of the first symptom of WS, whatever it may be. These data will be based solely on patient self-reporting. We have no way to increase the reliability of this data. However, this limitation will be taken into account in the analysis. We will collect the LogMAR far best corrected visual acuity at four or one meters according to the number of letters read.

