Furthermore, we will conduct statistical tests to investigate a correlation between the presence of swallowing disorders, vesico-sphincter disorders, and sleep apnea and the ano-sphincteric disorders in order to determine if there is a neurodegenerative cause and specify its location as mentioned previously.

In addition, we will study and compare the type of mutations in the WFS1 gene in each patient within the two subgroups since it seems that the severity of WS can vary according to this factor ^7,16^. These mutations are recorded in the patients' files. Therefore, this study will not require any new genetic testing. At least, if the previous analyses are inconclusive, we will compare the duration and severity of diabetes between the groups.

Determining the pathophysiological mechanism of this symptom is essential in order to be able to propose more suitable therapies in the future to improve the quality of life of patients.

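### Files are kept only if the outcome is recorded, but the start of systematic enquiry is undated, so selection may inflate the affected share and could bias the symptom associations

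*Protocol article*

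**What the plan says.** The Patients section of the protocol article defines the source as "files of patients followed in the Reference Center for Rare Diseases in Ophthalmology since 2018" and the inclusion rule as "We will only retain files in which the presence or absence of sphincter disorders is clearly mentioned". It supports the rule by saying that "this symptom is systematically sought during consultations and day hospitalization by the referring physician of the Centre". The one weakness it concedes is that "there is a risk that some patients may not have declared it".

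The Introduction describes a different practice at the same centre. The symptom came to light through the patient association, and "These symptoms were never mentioned because the patients and their family were not specifically sought during consultations and were very embarrassed".

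Under Method, "we will divide the patients into two subgroups according to the presence or absence of ano-sphincteric disorders", and the analysis will "investigate a correlation between the presence of swallowing disorders, vesico-sphincter disorders, and sleep apnea and the ano-sphincteric disorders". Under Scientific rationale, a significant urinary association without signs of pons involvement is to be read as pointing to the lower spinal cord. If no clear association appears, the explanation moves to diabetes-related dysautonomia.

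**The concern.** The two accounts of enquiry are compatible only if practice changed, and the article does not say when. The date matters because the retention rule works differently on each side of it.

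- **Once everyone is asked**, presence and absence are both written down. Dropping the few silent files does little harm.
- **Before that**, a presence is recorded if the patient raised it, but an absence is unlikely to be recorded at all. Patients whose last visit fell in such a period enter mainly as cases, and their unaffected counterparts are lost.

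The conceded limitation covers patients who are asked and do not declare the symptom. That is misclassification within the retained files. The loss of silent files is a separate selection problem and is not acknowledged.

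Two things are at stake: the affected share of the retained set and, under a further condition, the symptom associations from which the lesion is to be located. The Statistics section itself calls the sample small, so a moderate shift in an odds ratio could change which mechanism is reported.

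The inclusion sentence also says sphincter disorders without the prefix *ano-*. Read literally, a file recording only bladder sphincter status could qualify.

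**Working it through.** **1. The plan's own figures.** Scientific rationale reports 17 affected among 25 answers and 37 patients contacted: 17/25 = 68.00% and 17/37 = 45.95%. Both reproduce. They concern non-response to a questionnaire, not retention of files. They show only how far the handling of unknown status can move the affected share (68.00 − 45.95 = 22.05 percentage points).

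**2. Effect on the affected share.** The documents give no retention rates, so these are assumptions. Let *a* be the chance of being asked, the same for all patients, and *v* the chance that an unasked affected patient volunteers the symptom. Unasked unaffected patients leave no entry. An affected file is retained with probability a + (1 − a)v, an unaffected file with probability a. Take a true share of 17/37 and a = 0.5:

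| v | Affected retained | Unaffected retained | Affected share |
|---|---|---|---|
| 0 | 17 × 0.50 = 8.50 | 20 × 0.5 = 10 | 8.50/18.50 = 46% |
| 0.2 | 17 × 0.60 = 10.20 | 10 | 10.20/20.20 = 50% |
| 0.5 | 17 × 0.75 = 12.75 | 10 | 12.75/22.75 = 56% |
| 1 | 17 × 1.00 = 17.00 | 10 | 17.00/27.00 = 63% |

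**3. When the odds ratio is affected.** Let r(y,u) be the retention probability for outcome y and urinary status u. Then

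observed OR = true OR × [r(1,1) × r(0,0)] / [r(1,0) × r(0,1)].

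The factor equals 1 in each of these cases:
- Retention depends on outcome only (0.9 affected, 0.5 unaffected): (0.9 × 0.5)/(0.9 × 0.5) = 1.00.
- Retention depends on urinary status only (0.9 with, 0.5 without): (0.9 × 0.5)/(0.5 × 0.9) = 1.00.
- Retention depends on both, multiplicatively (0.9, 0.6, 0.6, 0.4): (0.9 × 0.4)/(0.6 × 0.6) = 1.00.

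Only a joint, non-multiplicative dependence moves it.

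**4. One such mechanism.** Suppose patients with urinary disorders are asked about bowel control in 80% of cases and the others in 40%, with *v* the same in both groups. The factor is

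[(0.8 + 0.2v) × 0.4] / [(0.4 + 0.6v) × 0.8].

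| v | Calculation | Factor |
|---|---|---|
| 0 | 0.320/0.320 | 1.00 |
| 0.1 | 0.328/0.368 | 0.89 |
| 0.2 | 0.336/0.416 | 0.81 |
| 1 | 0.400/0.800 | 0.50 |

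**5. A mechanism in the other direction.** If recording is better only when both symptoms coexist (0.9, against 0.5 in the other three cells), the factor is (0.9 × 0.5)/(0.5 × 0.5) = 1.80.

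**The case against.** The strongest reply is that much of the chain is not in the documents.

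- **Dates.** Nothing dates the patient association's report or the start of systematic enquiry, so a reader cannot state that the window from 2018 contains a period without enquiry. This stands. The Abstract's description of the symptom as recently recognised, and the 2025 date of the preliminary study, make it a reasonable suspicion and no more.
- **Files are not visits.** A patient first seen before enquiry began and still followed afterwards can have an entry. This stands. The loss falls on patients last seen before the change, and the documents do not say how many there were.
- **Urinary complaints as the trigger.** A reader might infer that bladder symptoms prompt the bowel question and that the urinary odds ratio is therefore pulled down, even halved. The documents do not support this. Scientific rationale says only that the two complaints resemble each other. Halving also requires every unasked affected patient to volunteer, whereas the Introduction says patients had not dared to raise the subject. That points to low volunteering and a factor nearer 1.
- **The rule treats presence and absence alike.** This is correct as written: it selects on the outcome being recorded, not on its value. Bias needs unequal recording, which is likely without enquiry but is not documented.
- **Prevalence is not the planned analysis.** True. An inflated affected share does not by itself bias the association tests.
- **Requiring a known outcome is ordinary practice.** Also true, and reading silent files as negative would be worse. That is no reason to leave the selection undescribed. The inclusion rule and its justification are fixed in the article itself, so this is not merely detail left to a fuller document.

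**Conclusion.** The point holds as a limited, conditional concern. What the text establishes is that entry depends on the outcome being recorded, that the rule is defended by systematic enquiry, that enquiry was earlier absent, that the change is undated, and that the loss of silent files is not acknowledged.

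If the change falls after the window opens and some unasked affected patients volunteered the symptom, the affected share is inflated: from 46% to between 50% and 63% for volunteering of 20% to 100%, with half of patients asked. The symptom associations are biased only if recording depends jointly on bowel and urinary (or other neurological) symptoms. On the assumed 80%/40% asking rates the factor runs from 1.00 to 0.50, and another plausible pattern gives 1.80. Neither the existence nor the direction of this bias can be settled from the documents. All these sizes rest on assumed rates. The change is still worth making, because it is cheap and protects the tests on which the location of the lesion depends.

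**What to change.** 1. State the date on which systematic enquiry began.
2. If that date is after the window opens, base the main analysis on all Wolfram patients of the Centre with at least one visit on or after it, and keep the full window since 2018 as a sensitivity set.
3. Reword the inclusion rule so that the recorded item must be ano-sphincteric status.
4. Report the number of files dropped for unknown status, and compare their urinary, swallowing, sleep apnea and disease-duration data with those of retained files.
5. Repeat each symptom test with the dropped files set to all affected and then to all unaffected. These runs are reference points, not strict limits on an odds ratio.
6. Do not fill silent files with questionnaire answers in the main outcome. The questionnaire is a different method of ascertainment, and its reported count combines fecal incontinence with constipation.

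The cost is some protocol wording, a count of files and a few re-runs on data already held. The downside is that some patients last seen before systematic enquiry leave the main set, in a study that is already small.

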## Method

The method we intend to implement will be based on data from literature concerning the possible neurological origin of fecal incontinence. A neurological mechanism will be considered given the pathophysiology of WS, which is a neurodegenerative condition (Barrett et al., 1993, Barrett and Bundey, 1997, Urano, 2016). It is well known that neurological or ENT symptoms, such as swallowing disorders, will appear during the course of WS (Marshall et al., 2013). However, in order not to overlook variations related to patient mutations, we will add to this study a genetic component. Marshal and other authors demonstrated that the severity of the symptoms during WS is related to the type of mutations harbored by the patients (Marshall et al., 2013)^.^.

In order to determine the mechanism of ano-sphincteric disorders, we will divide the patients into two subgroups according to the presence or absence of ano-sphincteric disorders.

According to this generic mechanism, we will collect different parameters that will be used in the analyses: the duration of the WS, the duration of insulin type I diabetes, the values of glycosylated hemoglobins over this period, the age of patients as well as their visual acuity at first occurrence of ano-sphincteric disorders and the presence of vesico-sphincter disorders, swallowing disorders or sleep apnea (Hoekel et al., 2014).

Firstly, we intend to characterize the severity of the WS in each patient as the occurrence of ano-sphincteric disorders. To that end, we have planned to consider more specifically three parameters from patient’s files for a multi-factorial analysis. We will consider the age of our patients when ano-sphincteric disorders were mentioned for the first time as well as the duration of WS and the duration of insulin type I diabetes at the time of the first mention of this symptom. This duration will be calculated from the age of the first symptom of WS, whatever it may be. These data will be based solely on patient self-reporting. We have no way to increase the reliability of this data. However, this limitation will be taken into account in the analysis. We will collect the LogMAR far best corrected visual acuity at four or one meters according to the number of letters read.

Furthermore, we will conduct statistical tests to investigate a correlation between the presence of swallowing disorders, vesico-sphincter disorders, and sleep apnea and the ano-sphincteric disorders in order to determine if there is a neurodegenerative cause and specify its location as mentioned previously.

In addition, we will study and compare the type of mutations in the WFS1 gene in each patient within the two subgroups since it seems that the severity of WS can vary according to this factor ^7,16^. These mutations are recorded in the patients' files. Therefore, this study will not require any new genetic testing. At least, if the previous analyses are inconclusive, we will compare the duration and severity of diabetes between the groups.

Determining the pathophysiological mechanism of this symptom is essential in order to be able to propose more suitable therapies in the future to improve the quality of life of patients.

## Ethics statement

According to national rules, patients were previously informed that their data could be anonymized and used for such type of study and their consent was considered as obtained if they did not specify their opposition.

The Ethic Committee of the French Ophthalmological Society approved this retrospective study, which adheres to the tenets of the Declaration of Helsinki. It is registered in Clinical trial under the number NCT07313085.

## Conclusion

WS is a neurodegenerative disease. Therefore, it is logical to assume that the origin of the ano-sphincteric disorders is linked to a reduction in pons volume or to damage to the sphincter control pathways in their terminal portion. However, the type of mutation, which explains the severity of the disease, could also be a factor. Finally, dysautonomic disorders may be considered. In any case, the management of these ano-sphincteric disorders is difficult. in the literature it requires methods ranging from the simplest to more complex techniques for restoring transit control (Emmanuel, 2010). Understanding the mechanism of this symptom is not trivial and will have an impact on the therapies that may or may not be offered.

